Additionally, neurophysiological predictors of treatment outcome will be investigated. Target parameters of the baseline NIRS and EEG assessments will be used as predictors in regression analyses. Based on previous findings regarding the prediction of treatment outcome via EEG markers of frontal lobe function in schizophrenic patients [50], we expect treatment effects to be particularly pronounced in participants with weak activation in the baseline frontal lobe assessments, especially for the NIRS feedback arm that is specifically focused on strengthening frontal lobe function. Regarding the EEG baseline data, mean relative theta and relative beta power as well as theta/beta ratios will be calculated for frontal and central regions of interest (ROI) during the eyes open and eyes closed resting state conditions. Additionally, P300 and CNV amplitudes and latencies will be calculated during neuropsychological assessment. Research indicates that adult ADHD participants possess elevated theta/beta ratios [13,14], which have been found to discriminate ADHD participants from healthy control populations [51,52]. These ratios may have prognostic value for prediction of outcome after stimulant medication as well as after neurofeedback treatment [18]. Elevated theta/beta ratios are hypothesized to reflect task-related brain “activation” and serve as a discriminant of behavioral performance [53]. Dominant slow wave activity has been linked with reduced auditory oddball P300 activity [54] and stimulant medication response [52], while larger pre-training CNV activation has been linked with larger symptom reductions following SCP feedback [55]. Therefore, we expect effects to be particularly pronounced in participants with elevated theta/beta ratios and decreased P300 amplitude but greater CNV negativity at baseline assessment.

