## Methods/Design

In this proof-of-principle study, a total of 60 adult participants diagnosed with ADHD (combined, hyperactive, or inattentive type) are randomly blockwise assigned to SCP, NIRS, or electromyogram (EMG) feedback groups (n = 20 each) stratified for age, sex, and educational level. This is the first study to investigate and compare the efficacy of these treatment modalities in an adult ADHD population.

Twenty healthy controls matched for age, sex, IQ, and pre- and post-treatment duration will be included in the neurophysiological assessments for pre- and post-treatment measurement in order to establish “expected” activation patterns and allow for a more thorough interpretation of changes following the neurofeedback treatment. The study objectives are as follows:Assess whether there are physiological differences (EEG and ERP) in ADHD participants compared to healthy controls.Assess whether adult participants are able to demonstrate learning of cortical self-regulation.Assess whether treatment leads to an improvement in cognition (that is, attention and working memory) and behavior (that is, restlessness and impulsivity), and changes in specific EEG or NIRS parameters.Assess whether specific methods and protocols are more efficacious in changing behavioral, cognitive, and EEG and NIRS outcome variables.Assess whether changes are stable at the 6-month follow-up.Assess whether specific methods and protocols differ in the stability of cortical self-regulation and clinical effects at the 6-month follow-up.Assess whether the efficiency of the different training protocols differs depending on individual neurocognitive baseline parameters (for example, frontal lobe activation during neuropsychological assessments; baseline CNV etc.).

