### Statistics

#### Sample-size calculation

The basic problem with determining the number of cases needed is that there are no comparable studies about SCP training in adults and even fewer studies about the influence of the blood flow regulation. For this study, the planned sample size is based on a power calculation of a meta-analysis by Arns *et al*. [75] that showed a grand mean effect size of 0.81 for improvements in inattention in children with ADHD by EEG neurofeedback training as compared to passive or semi-active (for example, EMG) placebo trainings. Assuming a pre-defined α of 0.05, a power criterion of at least 80%, and one-sided testing, such an effect size would indicate a required sample size of n = 20 per treatment group.

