#### Neurophysiological predictors

To investigate neurophysiological predictors of treatment outcome, target parameters of the baseline NIRS, EEG, and peripheral physiology data assessments will be analyzed in all treatment groups (SCP, NIRS, and EMG). Specific to the NIRS assessment parameters, mean task-related activation (changes in the concentration of O_2_Hb and HHb) during the baseline assessment will be individually calculated for both the 2-back condition of the working memory (n-back) task and the NoGo condition of the Go-NoGo paradigm. Specific to the EEG assessment parameters, like mean relative theta and relative beta power and theta/beta ratios will be calculated for frontal and central ROIs during eyes open and eyes closed resting state conditions. Additionally, P300 and CNV amplitudes and latencies for these ROIs will be calculated during neuropsychological assessments. The peripheral data from heart rate, respiration, and SCL will be used to assess the peripheral arousal during active (ERP tasks) and resting (eyes open/eyes closed) conditions. These parameters will then be used as independent variables in a regression analysis to predict treatment success (as indicated by changes in psychometric scores in the ADHD symptom scales).

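### The predictor regression does not match the objective of asking whether each protocol's effect depends on baseline, and about 30 candidate predictors are too many for 60 participants in any form the text allows

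*Protocol article*

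**What the plan says.** Methods/Design ends its list of objectives with this one: "Assess whether the efficiency of the different training protocols differs depending on individual neurocognitive baseline parameters". The Background gives directional hypotheses. Treatment effects should be larger where baseline frontal activation is weak, above all in the NIRS arm, and it adds that "we expect effects to be particularly pronounced in participants with elevated theta/beta ratios and decreased P300 amplitude but greater CNV negativity at baseline assessment".

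The Neurophysiological predictors section lists task-related O2Hb and HHb changes, resting theta and beta measures, P300 and CNV amplitudes and latencies, and heart rate, respiration and skin conductance, for all three arms. It then states: "These parameters will then be used as independent variables in a regression analysis to predict treatment success (as indicated by changes in psychometric scores" on the symptom scales. No other independent variable is named. The Abstract speaks of regression models in the plural.

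The sample is "a total of 60 adult participants diagnosed with ADHD", in "feedback groups (n = 20 each) stratified for age, sex, and educational level".

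**The concern.** Whether a protocol works better in people with a given baseline profile is a question about differences in slope between arms. A regression whose independent variables are baseline parameters alone, fitted over all arms, estimates who improves under any training, including the EMG control that is there to capture nonspecific effects. It cannot separate a predictor of response to NIRS or SCP feedback from a general prognostic marker.

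The list is also long for the sample, and the section names no step that shortens it. If it is followed as written, chance associations are likely to look like predictors, and the arm-specific hypothesis would have no formal comparison behind it.

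**Working it through.** **1. The plan's own figure.** The Sample-size calculation section assumes an effect of 0.81: "Assuming a pre-defined α of 0.05, a power criterion of at least 80%, and one-sided testing". Normal approximation: n = 2 x (1.645 + 0.842)^2 / 0.81^2 = 18.9, so 19 per group. The exact one-sided t calculation gives 20 per group, with power 0.808. The stated 20 reproduces, but it covers a two-group comparison of means and says nothing about the regression.

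**2. Predictor count, from the Neurophysiological predictors section.**

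| Block | Product | Count |
|---|---|---|
| NIRS | 2 chromophores x 2 tasks | 4 |
| Resting EEG | 3 measures x 2 regions x 2 eye conditions | 12 |
| ERP | 2 components x 2 features x 2 regions | 8 |
| Peripheral | 3 measures x 2 states | 6 |
| Total | | 30 |

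With one value per peripheral measure the total is 4 + 12 + 8 + 3 = 27. With NIRS split left and right (8), P300 taken from two tasks (ERP 12) and eyes open and closed kept apart for the peripheral data (9), it is 8 + 12 + 12 + 9 = 41.

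**3. Reading A: one pooled model, joint entry, n = 60.** Residual df = 60 - 30 - 1 = 29. With no true association, expected R-squared = p/(n - 1) = 30/59 = 0.51 (27/59 = 0.46 and 41/59 = 0.69 at the ends of the range). In simulation with independent noise predictors, about 65% of such models had at least one coefficient with p < 0.05. If three predictors truly explain 20% of the variance, the 30-predictor model shows an apparent R-squared of 0.61 and a new-sample R-squared of about -0.70. A model with those three alone gives 0.24 and 0.14.

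Pooling also hides moderation. With assumed arm slopes of 0, -0.6 and +0.6, the pooled slope was significant in only 7% of simulated trials, close to the 5% expected by chance.

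**4. Reading B: separate models by arm, joint entry, n = 20.** Residual df = 20 - 30 - 1 = -11. There is no unique fit; even the low count of 27 exceeds 20.

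**5. Reading C: one predictor at a time.** There is no overfitting, but with 30 independent tests at 0.05 the familywise error is 1 - 0.95^30 = 0.79 per symptom scale. The endpoints section names three symptom scales: 1 - 0.95^90 = 0.99 over 90 tests. Without an arm term, the single tests are still not tests of moderation.

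**6. Would adding interactions to the full list help?** Intercept 1 + arm 2 + predictors 30 + interactions 60 = 93 coefficients on 60 participants. No. With q predictors the model has 3 + 3q coefficients, so q = 19 already leaves no residual df. One predictor per model uses 6 and leaves 54.

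**7. What one arm-by-predictor model can detect.** The standard error of a slope difference between two arms of 20 is about sqrt(2/17) = 0.343 residual SD per predictor SD. For 80% power, two-sided:

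- alpha 0.05: (1.960 + 0.842) x 0.343 = 0.96
- alpha 0.0125 (0.05/4, the first Holm step over four tests): (2.498 + 0.842) x 0.343 = 1.15

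Simulating the 2-df interaction test, with the slope differing in one arm only, a difference of 0.96 had power of about 0.8 at alpha 0.05 but only about 0.65 at 0.0125. At 0.0125, about 1.1 to 1.15 is needed for 80%. At a difference of 0.5, power was about 0.30 even at alpha 0.05. These slopes are assumptions; the article gives none.

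**The case against.** The article does not fix the model. It does not say that the parameters enter together, that the arms are pooled or that arm is left out. The Abstract's plural, and the phrase about all treatment groups, both leave room for fits by arm. A condensed article may leave the arm term, the selection of variables and multiplicity to an analysis plan. The three failures in the working belong to three different readings and cannot all be faults of one analysis. The predictor list is partly illustrative, so 30 is a reconstruction. The study calls itself proof of principle, and these regressions support no primary or secondary endpoint.

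Most of this stands as a limit on what can be claimed. A reader might infer that the plan is definitely one pooled main-effects regression; the text does not establish that. A reader might also infer that the NIRS hypothesis goes untested. Under fits by arm it would be examined within the NIRS arm, though without a comparison of slopes. Two further inferences do not hold. Regression to the mean from unadjusted change scores rests on silence, since the article neither includes nor excludes the baseline score. The theta/beta ratio is a nonlinear function of the two powers, so it is not exactly collinear with them.

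The objection does not remove the mismatch. The article commits to an objective and to a predictor list for it, and no available reading of that list answers the objective soundly.

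**Conclusion.** The point holds as a mismatch between a stated objective and the stated analysis, together with a predictor list too long for the sample. It does not hold as a claim that one particular faulty model has been fixed.

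Its size depends on the reading: expected null R-squared of 0.51 pooled (0.46 to 0.69 over the range of counts), no unique fit within an arm, or about 79% familywise error per scale when tested singly. The R-squared figure assumes that all parameters enter jointly and that all 60 participants have complete data. The 79% assumes independent tests; these measures are likely to be correlated, which would lower it. The matter affects a secondary objective and not the primary comparison, so it should be corrected but does not threaten the trial's main result.

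**What to change.** Replace the open list with four pre-specified predictors that match the Background hypotheses: theta/beta ratio, P300 amplitude, CNV amplitude, and one measure of baseline frontal activation. The Background names no specific frontal measure, so the sponsor should choose one from the Neurophysiological predictors section, for example O2Hb in the 2-back or the NoGo condition. Region and recording condition should be fixed for each predictor, and one symptom scale named as the outcome.

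For each predictor, fit one model in all 60 participants: post-test symptom score on baseline score, arm, predictor and arm-by-predictor. Test the interaction (2 df) and apply Holm over the four.

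Label all other parameters exploratory, for example in one penalised model reported with cross-validated R-squared.

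State that with 20 per arm, 80% power is reached only for slope differences of about 0.96 residual SD per predictor SD at unadjusted alpha 0.05, and about 1.1 to 1.15 at the first Holm step (0.0125), so the results are hypothesis-generating.

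The change is to analysis wording only; no data collection is affected. The cost is that fewer predictors can be called confirmatory, and even those four have little power for moderate slope differences.

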#### Training-data

Session 1 will be discarded because it is assumed that participants still have to habituate to the setting. NIRS, SCP and EMG feedback data will be analyzed to determine:If participants in treatment groups are able to learn self-regulation of the trained parameter over the course of treatment and at 6-month follow-up.If the difference between activation and deactivation changes throughout treatment.Further, the participants will be divided into learners and nonlearners of self-regulation for further analysis.

### Slow cortical potential group

For each participant, mean differences between SCP amplitudes during both tasks (negativity/positivity) will be calculated. The differences between SCP amplitude in activation and deactivation will be analyzed separately over the cause of treatment to assess the acquired self-regulation abilities. This will be analyzed for feedback and transfer conditions.

### Electromyogram group

Data will be analyzed in the same manner as the SCP data.

### Near-infrared spectroscopy group

Hemodynamic responses will be quantified for tasks (activation/deactivation/rest), conditions (feedback/transfer) and over the course of treatment. Differences between hemodynamic response amplitudes in activation versus deactivation (as well as rest) trials will be analyzed separately for each assessment point. Changes in the hemodynamic responses for activation and deactivation trials over time (as well as changes in the difference of activation versus deactivation trials) will be analyzed and computed for both feedback and transfer conditions.

## Discussion

This paper presents the protocol and design of a randomized controlled trial with two types of neurofeedback (SCP and NIRS) and an active control (EMG biofeedback) condition for adults with ADHD. This is the first study to systematically investigate neurofeedback in adults with ADHD. It is also the first study to compare SCP and NIRS feedback to an active control condition on the one hand and to investigate this in an adult ADHD population on the other hand.

If one or both feedback types are superior to the control condition, a first step will be made towards a new acknowledged treatment option for adult ADHD.

This is not the “gold standard” design for treatment studies, which is a placebo-controlled randomized double blind design [76]. The problems with this approach are widely discussed elsewhere [77,78]. Therefore, to allow for all therapeutic aspects of neurofeedback therapy to come into effect, such as a good patient-therapist relationship, psychoeducation, and strengthening of self-efficacy expectations, we decided to use an active control condition that was used in other studies before. The study design was based on a study protocol of a multicenter treatment study with ADHD children [57]. The use of EMG feedback as an active control condition is based on the rationale that EMG feedback is not an “empty” treatment, but will induce identical nonspecific (placebo) effects that will help to differentiate between specific effects of the neurofeedback and nonspecific effects from the above-mentioned aspects.

### Possible limitations

As this study is being conducted with adults, we did not implement transfer exercises from the study on children [57] in which the children performed homework in combination with transfer trials in the lab. We also did not include a token system in which good cooperation was rewarded with stickers that the children were able to exchange for little presents or coupons. Whether this motivational aspect should have been implemented, remains open.

The results of this study are important in several aspects. First, there is a need for more research in the field of adult ADHD and especially in the field of neurofeedback treatment for adult participants with ADHD. ADHD changes its characteristics with maturation, and therefore, findings from a childhood population have only a limited impact on adult ADHD research. Second, NIRS feedback is a new and potentially more time-efficient type of self-regulation therapy. To date, an investigation and comparison of SCP and NIRS feedback training to an active control has not been conducted; therefore, we hope to gain valuable insights in effects and differences of these types of treatment for ADHD in adults.

## Trial status

The trial is ongoing.

## Abbreviations

ADHD: Attention-deficit hyperactivity disorder
ADHD-SB: ADHS Selbstbeurteilungsskala
ANOVA: Analysis of variance
BDI-II: Beck’s depression inventory
BSL-23: Borderline symptom list
BOLD: Blood-oxygen-level dependent
CFT 20-R: Culture fair test-20 revised
CNV: Contingent negative variation
DLPFC: Dorsolateral prefrontal cortex
d2-R: Test of attention
ECG: Electrocardiogram
EEG: Electroencephalogram
EHI: Edinburgh handedness inventory
EMG: Electromyogram
ERP: Event-related potential
FEA-FFB and FEA-AFB: Fragebogen zur Erfassung von ADHS im Erwachsenenalter, frühere/aktuelle Probleme - Fremdbeurteilung (German ADHD third-party rating scale)
fMRI: Functional magnetic resonance imaging
FERT: Fragebogen zur Erfassung relevanter Therapiebedingungen (German Therapy Effect Rating Scale)
fNIRS: Functional near-infrared spectroscopy
HHb: Deoxygenated hemoglobin
NIRS: Near-infrared spectroscopy
O2Hb: Oxygenated hemoglobin
PANAS: Positive affect negative affect schedule
PFC: Prefrontal cortex
PPI: Psychopathic personality inventory
RT: Reaction time
Q: Questionnaire
ROI: Region of interest
SCID: Structured clinical interview for DSM-IV disorders
SCL: Skin conductance level
SCP: Slow cortical potential
STAI: State-trait anxiety inventory
WRI: Wender-reimherr interview
WURS-K: Wender utah rating scale
